## PROTOCOL VERSIONS

| Version # | Date       | Amendment # | Reasons for the update                     |
|-----------|------------|-------------|--------------------------------------------|
| 1.0       | 31/03/2020 |             |                                            |
| 1.1       | 04/04/2020 | -           | Response to the ethic committee's comments |
| 1.2       | 08/04/2020 | -           | Response to ANSM comments                  |

---

## ABBREVIATIONS

|        |                                                        |
|--------|--------------------------------------------------------|
| AE     | Adverse Event                                          |
| ALT    | Alanine aminotransferase                               |
| ANRS   | French Agency for Research on AIDS and Viral Hepatitis |
| AR     | Adverse Reaction                                       |
| AST    | Aspartate aminotransferase                             |
| AUC    | Area Under a Curve                                     |
| BIS    | " Bis in die " (twice a day)                    |
| CHU    | University Hospital Center                             |
| CRA    | Clinical Research Assistant                            |
| CRF    | Case Report Form                                       |
| CTU    | Clinical Trial Unit                                    |
| D      | Day                                                    |
| DNA    | Deoxyribonucleic acid                                  |
| DSMB   | Data & Safety Monitoring Board                         |
| eTMF   | electronic Trial Master File                           |
| ICH    | International Council on Harmonization                 |
| INSERM | National Institute of Health and Medical Research      |
| ITT    | Intent-to-treat analysis                               |
| PP     | Per protocol analysis                                  |
| QD     | " Quaque die " (once a day)                     |
| RNA    | Ribonucleic acid                                       |
| SAB    | Scientific Advisory Board                              |
| SAE    | Serious Adverse Event                                  |
| SAR    | Serious Adverse Reaction (Serious Adverse Reaction)    |
| SDPM   | See Details Procedures Manual                          |
| SOP    | Standard Operating Procedure                           |
| SPC    | Summary of product characteristics                     |
| SUSAR  | Suspected Unexpected Serious Adverse Reaction          |
| WHO    | World Health Organization                              |

**SUMMARY**

|                                      |                                                                                                                                                                                                                                                                                                                                                                                                                                                                                                                                                                                                                                                                                                                                                                                                                                                                                                                                                                                                                                                                                                                                                                                                                                                                                                                                                      |
|--------------------------------------|------------------------------------------------------------------------------------------------------------------------------------------------------------------------------------------------------------------------------------------------------------------------------------------------------------------------------------------------------------------------------------------------------------------------------------------------------------------------------------------------------------------------------------------------------------------------------------------------------------------------------------------------------------------------------------------------------------------------------------------------------------------------------------------------------------------------------------------------------------------------------------------------------------------------------------------------------------------------------------------------------------------------------------------------------------------------------------------------------------------------------------------------------------------------------------------------------------------------------------------------------------------------------------------------------------------------------------------------------|
| SPONSOR                       | CHU de Bordeaux                                                                                                                                                                                                                                                                                                                                                                                                                                                                                                                                                                                                                                                                                                                                                                                                                                                                                                                                                                                                                                                                                                                                                                                                                                                                                                                                      |
| COORDINATING INVESTIGATOR     | [name]                                                                                                                                                                                                                                                                                                                                                                                                                                                                                                                                                                                                                                                                                                                                                                                                                                                                                                                                                                                                                                                                                                                                                                                                                                                                                                                                          |
| TITLE                         | Home treatment of elderly patients with symptomatic SARS-CoV-2 infection (COVID-19) : a multiarm, multi-stage (MAMS) randomized trial to assess the efficacy and safety of several experimental treatments to reduce the risk of hospitalization or death (COVERAGE trial)                                                                                                                                                                                                                                                                                                                                                                                                                                                                                                                                                                                                                                                                                                                                                                                                                                                                                                                                                                                                                                                                           |
| BACKGROUND                    | In adults aged 65 years or older with COVID-19 disease without hospitalization criteria, early treatment could prevent hospitalization or death. No treatment is currently validated for this indication.                                                                                                                                                                                                                                                                                                                                                                                                                                                                                                                                                                                                                                                                                                                                                                                                                                                                                                                                                                                                                                                                                                                                            |
| MAIN OBJECTIVE                | To estimate the efficacy of several specific experimental treatments, compared to standard care, to prevent hospitalization or death at D14 in adults over 65 years of age, with documented SARS-CoV-2 infection, with symptoms lasting less than 72 hours and not meeting any hospitalization criteria.                                                                                                                                                                                                                                                                                                                                                                                                                                                                                                                                                                                                                                                                                                                                                                                                                                                                                                                                                                                                                                             |
| BENEFITS FOR THE PARTICIPANTS | Daily follow-up by a dedicated team.                                                                                                                                                                                                                                                                                                                                                                                                                                                                                                                                                                                                                                                                                                                                                                                                                                                                                                                                                                                                                                                                                                                                                                                                                                                                                                                 |
| DESIGN                        | Phase III multi-centre, open-label, randomized controlled superiority multi-arm multi-stage, (MAMS) trial                                                                                                                                                                                                                                                                                                                                                                                                                                                                                                                                                                                                                                                                                                                                                                                                                                                                                                                                                                                                                                                                                                                                                                                                                                            |
| INCLUSION CRITERIA            | 
 
– Positive SARS-CoV-2 test on nasopharyngeal swab
 
– Onset of symptoms < 72 hours prior to nasopharyngeal swabbing
 
– Age ≥ 65 years old
 
– Valid, ambulatory person, fully capable of understanding the challenges of the trial
 
– No hospitalization criteria according to current recommendations
 
– Signed informed consent
 
– Covered by Health Insurance
 
                                                                                                                                                                                                                                                                                                                                                                                                                                                                                                                                                                                                                                                                                                                                                                                                                                                                                  |
| EXCLUSION CRITERIA            | 
 
– Inability to make a decision to participate (dementia, guardianship)
 
– Long QT syndrome, or QTc space > 500 ms
 
– Presence of a pace maker
 
– Heart rate <50 / min
 
– Hyperkalaemia > 5.5 mmol/L or hypokalaemia < 3.5 mmol/L
 
– Treatment with piperazine, halofantrine, dasatinib, nilotinib, citalopram, escitalopram, hydroxyzine, domperidone, potent inhibitors of cytochrome P450 CYP3A4 isoenzyme, potent inducers of cytochrome P450 CYP3A4 isoenzyme repaglinide, azathioprine, 6-mercaptopurine, theophylline, pyrazinamide, warfarin
 
– Hypersensitivity to any of the test drugs or chloroquine and other 4-aminoquinolines, amodiaquine, mefloquine, glafenine, floctafenine, antrafenine, ARB or sartan.
 
– Hepatic porphyria, known obstructive hepato-biliary disease, liver failure (stage ≥ Child-Pugh B), stage 4 or 5 chronic kidney disease (DFG <30 mL/min/1.73 m^2) or person on dialysis, retinopathy, lactose hypersensitivity, abnormalities in galactose metabolism, lactase deficiency, malabsorption syndrome, known glucose-6-phosphate dehydrogenase deficiency, symptomatic gout/hyperuricemia, ileus, colitis or enterocolitis, chronic infection with the hepatitis B virus
 
 |
| TREATMENTS                    | 
 
– AZINC Forme et Vitalité®: (comparator ; vitamins + trace elements complex)
 
– Plaquenil® (Hydroxychloroquine)
 
                                                                                                                                                                                                                                                                                                                                                                                                                                                                                                                                                                                                                                                                                                                                                                                                                                                                                                                                                                                                                                                                                                                                                                            |

|                                                                            |                                                                                                                                                                                                                                                                                                                                                                                                                                                                                                                                                                                                                 |
|----------------------------------------------------------------------------|-----------------------------------------------------------------------------------------------------------------------------------------------------------------------------------------------------------------------------------------------------------------------------------------------------------------------------------------------------------------------------------------------------------------------------------------------------------------------------------------------------------------------------------------------------------------------------------------------------------------|
|                                                                            | 
 
- Avigan® (Favipiravir)
 
- Imatinib TEVA®
 
- Micardis® (Telmisartan)
 
 
Treatments will be given for 10 days. People who were on angiotensin conversion enzyme inhibitor (ACEI) or ARB treatment before inclusion will not be randomized to the Telmisartan arm
                                                                                                                                                                                                                                                                           |
| MAIN OUTCOME                                                        | Proportion of participants with an occurrence of hospitalization and/or death between D0 and D14 in each arm                                                                                                                                                                                                                                                                                                                                                                                                                                                                                                    |
| NUMBER OF CENTERS                                                   | The study takes place on an outpatient basis with follow-up at home and by telephone.                                                                                                                                                                                                                                                                                                                                                                                                                                                                                                                           |
| DURATION                                                            | 
Inclusion period: 3 months
 
Participation duration: 28 days.
                                                                                                                                                                                                                                                                                                                                                                                                                                                                                                                                       |
| ANALYSIS                                                            | 
This is a Phase III trial. Sequential analyses will be performed for the primary endpoint at D14, with the following objectives:
 
 
- Intermediate analysis #1 (30 included patients per arm): futility
 
- Intermediate analysis n°2 (60 patients included per arm): futility
 
- Intermediate analysis n°3 (102 patients included per arm): futility and early efficacy
 
- Final analysis: efficacy
 
                                                                                                                               |
| NUMBER OF PARTICIPANTS                                              | 
 
- 169 participants in each of the 5 arms in people who were not on basic therapy with IEC or ARA2 before inclusion, i.e. 845 patients in total if the 5 arms are maintained until the end.
 
- 53 participants in each of the 4 arms (excluding telmisartan) in people who were on treatment with IEC or ARA2 before inclusion, i.e. 212 more patients if the 4 arms are maintained until the end.
 
 
The final number will depend on the number of arms that will continue after the intermediate analyzes and could not exceed 1057 participants
 |
| EXPECTED BENEFITS                                                   | Treatments to prevent complications of COVID-19 in the elderly. French hospitals are overwhelmed with new COVID-19 patients and it is expected that beds in the intensive care units will run out in the near future. Finding an effective treatment that can be administered at home to avoid hospitalization and transfer to intensive care is of critical importance.                                                                                                                                                                                                                                        |
| SIMULTANEOUS PARTICIPATION IN ANOTHER RESEARCH AND EXCLUSION PERIOD | 
The inclusion and simultaneous participation in any other interventional study is not authorized in order not to interfere with the results of this research.
 
No exclusion period is necessary following this research.
                                                                                                                                                                                                                                                                                                                                                                           |

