#### 5.1.2 Non-inclusion criteria

##### 5.1.2.1 Autonomy

- Incapable of understanding the meaning of participating in the study (*i.e.*: dementia) or to make a decision to participate (*i.e.*: person under protection of justice, tutorship or guardianship).
- Person with a score  $\geq 7$  on the Rockwood Clinical Frailty Scale
- Chronic illness at a severe stage, with limited life expectancy.

In the particular case of people resident in a nursing home, opinion on inclusion from the coordinating physician of the facility shall be sought, with particular consideration to the environment and the practices at the nursing home.

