##### 5.1.2.2 Cardiovascular precautions

- An ECG shall be systematically carried out before inclusion.
  - In the case of known Long QT Syndrome, or QTc interval  $\geq 500$ ms in the ECG carried out before inclusion, that person shall not be included in the trial.
  - In the case of a QTc interval between 460 and 500ms in the ECG carried out before inclusion, or any significant anomaly in the ECG such as repeated ventricular extra-systoles, or any significant cardiovascular history giving grounds to believe a predisposition to rhythmic or conduction abnormalities, where the taking of study drugs could bring about conduction or rhythm problems, cardiological opinion shall be systematically sought before any decision to include [SDPM]. If the opinion is such of being capable of inclusion, that person shall be

subject to daily 6 lead ECG monitoring during the first seven days of treatment (please see paragraph **Erreur ! Source du renvoi introuvable.**).

- Blood electrolytes are not to be systematically analysed before inclusion. On the other hand:
  - If the person has benefited from blood electrolytes testing before inclusion (for example, because s/he has sought urgent consultation with symptoms leading to a blood electrolytes prescription), s/he shall not be included if serum potassium were  $>5.5$  mmol/L or  $<3.5$  mmol/L.
  - The results of the blood electrolytes testing performed at the time of inclusion (please see paragraph **Erreur ! Source du renvoi introuvable.**) shall be sent on immediately to the researchers. In cases of significant hypokalaemia, an appropriate decision shall be made in consultation with the researcher, cardiologist and attending physician.

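### The Summary's exclusion list is stricter than section 5.1.2: nine of its entries are missing from 5.1.2, two more are only partly covered, and the drug gap carries into the 10-day co-medication bar

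*Protocol*

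**What the plan says.** The protocol states its exclusions twice.

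**Summary, Exclusion criteria.** Besides the entries it shares with the body, this list contains:
- two cardiac entries: "Presence of a pace maker" and a heart rate below 50/min;
- six drugs at the end of the drug line: "repaglinide, azathioprine, 6-mercaptopurine, theophylline, pyrazinamide, warfarin";
- three illness entries at the end of the illness line: "ileus, colitis or enterocolitis, chronic infection with the hepatitis B virus".

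**Section 5.1.2, Non-inclusion criteria.** None of those 11 entries appears in 5.1.2.1 to 5.1.2.4. This section has two stand-alone criteria that the Summary lacks: a score of 7 or more "on the Rockwood Clinical Frailty Scale", and "Chronic illness at a severe stage, with limited life expectancy". For ECG anomalies or a relevant cardiovascular history, 5.1.2.2 requires that "cardiological opinion shall be systematically sought before any decision to include".

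**Section 5.2.6, Concomitant drugs.** Drugs that are non-inclusion criteria may not be prescribed for 10 days after inclusion. The paragraph reference that should identify the list is a broken field.

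No section says which list governs, or that both apply together.

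**The concern.** A summary may be shorter than the body it summarises. Here it is longer, and stricter, on 11 entries. A person taking warfarin, or with chronic hepatitis B, is excluded by one list and not by the other.

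Sections 5.2.6, 5.3.2 and 5.3.3 all speak of non-inclusion criteria, which is the title of 5.1.2 and not of the Summary list. Staff following the body could therefore enrol people whom the Summary excludes. Because 5.2.6 takes its bar from the same criteria, the six drugs would then also be open to prescription during treatment.

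The Summary gives no reasons for its entries, so a safety purpose is an inference. It is a reasonable one: section 1.4.3 names multiple drug treatments, interactions and cardiac toxicity as matters for particular attention in this population, which is aged 65 and over and treated at home. There is a reporting consequence too. Section 6.3.2 promises a description of deviations from eligibility criteria, and for these 11 entries it is unclear what counts as a deviation.

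**Working it through.** No sample-size, power or alpha figure is involved. The check is an item-by-item comparison of the Summary's exclusion list with 5.1.2.1 to 5.1.2.4. Colitis or enterocolitis is counted as one entry, and CYP3A4 inhibitors and inducers as one entry each.

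| Group | Summary | Section 5.1.2 | Only in Summary |
|---|---|---|---|
| Drugs (5.1.2.3) | 16 | 10 | 16 − 10 = 6 |
| Illnesses (5.1.2.4) | 14 | 11 | 14 − 11 = 3 |
| Pacemaker; heart rate below 50/min (5.1.2.2) | 2 | 0 | 2 − 0 = 2 |
| Total | | | 6 + 3 + 2 = 11 |

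Simple subtraction is valid because no drug and no illness is listed only in 5.1.2. If colitis and enterocolitis are counted separately, the total is 12.

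**Could the six drugs be covered indirectly?** Section 5.1.2.3 gives examples in brackets for its two CYP3A4 classes, and none of the six is among them. The Summary has no comma between the CYP3A4 inducer entry and the first of the six, so a reader might take them as examples of inducers. On that reading too, they are named in the Summary and not in 5.1.2.3.

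**Could the illnesses be covered indirectly?** The list in 5.1.2.4 ends at gout or hyperuricaemia. Ileus, colitis or enterocolitis, and hepatitis B are not in it.

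**Could the cardiac entries be covered indirectly?** Partly. Everyone has an ECG before inclusion, and 5.1.2.2 sends significant anomalies and relevant history to a cardiologist. That is referral with inclusion still possible, not exclusion. So 11 − 2 = 9 entries have no specific cover in 5.1.2, and 2 have partial cover.

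**Carry-over to 5.2.6.** If non-inclusion criteria means 5.1.2, the 10-day bar covers 10 of the 16 drug entries. If it means the Summary list, it covers all 16. The broken reference leaves this open.

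**Other direction.** Two stand-alone criteria are only in 5.1.2: the Rockwood score and limited life expectancy. The 30-day look-back for four drugs and hypersensitivity to excipients are also only there, but these refine criteria that both lists share.

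**Shared entries worded differently.**
- QTc: the Summary line beginning "Long QT syndrome, or QTc space" excludes strictly above 500 ms, while 5.1.2.2 excludes at 500 ms or more. They differ at one value.
- Potassium: both use above 5.5 or below 3.5 mmol/L. The Summary attaches no condition. Section 5.1.2.2 applies the limits to a result that already exists, and adds that "Blood electrolytes are not to be systematically analysed before inclusion".

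**The case against.** The strongest reply is that the body governs. Only 5.1.2 carries the title that the later sections use, and the broken reference is a formatting fault found throughout the protocol, so it says nothing particular about eligibility. This is fair as a reading, but it does not remove the problem. If 5.1.2 governs, the Summary states 11 exclusions that are not in force, and the six drugs are outside the co-medication bar.

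A second reply is to apply both lists, since section 9.5 allows no exemptions. That is a workable practice, but the protocol does not state it.

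A third is that safeguards exist. The ECG and cardiology referral do reduce the weight of the two cardiac entries. Section 5.3.3 requires a review of current treatments, but that review still needs a list to check against. The eCRF controls in 9.3.4 and the detailed procedures are not shown and may already settle the matter.

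Three stronger readings should be resisted:
- **Potassium as a direct contradiction.** A reader might infer one because the Summary's exclusion is unconditional. The cut-offs are identical, the Summary orders no test, and anyone with a known pre-inclusion result gets the same answer from both texts. Section 5.1.2.2 reads naturally as the operational form of the Summary line.
- **No response at all to high potassium on the Day 0 sample.** Sections 5.1.2.2 and 5.3.4 name only hypokalaemia when they describe a specific action. But 5.3.4 also has a sentence on interrupting the trial drug if the confirmed value calls for it, and that sentence is not limited to low values.
- **QTc as a headline conflict.** It concerns exactly 500 ms, and 5.1.2.2 is already the stricter text.

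The entries found only in 5.1.2 also carry less weight, because a summary may omit detail.

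**Conclusion.** The mismatch is certain as a matter of text and should be corrected. Its firm core is nine Summary exclusions (six drugs, three illness entries) with no specific cover in 5.1.2, plus two cardiac exclusions only partly covered. The drug gap extends to the 10 days after inclusion if 5.1.2 is the list meant in 5.2.6. Two stand-alone criteria are missing in the other direction.

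The consequence is less certain. The protocol supports saying that people could be enrolled or co-prescribed against its own Summary. It does not support saying that they would be, or that harm would follow, and it gives no basis for a number affected.

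A reader might also infer that the main result is at risk. It is not: the primary analysis is by intention to treat, and section 6 limits major eligibility deviations to the RT-PCR result and age. The stakes are participant safety and consistent enrolment.

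**What to change.** By amendment, use one identical list in the Summary, section 5.1.2 and the eCRF eligibility form:

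1. Add the 11 Summary-only entries to 5.1.2, unless the investigators and the safety unit record a reason to drop an item. Section 1.4.3 shows that the sponsor weighed the loss of eligible people when choosing treatments, so a reasoned deletion is legitimate.
2. Add the criteria found only in 5.1.2 to the Summary.
3. Point 5.2.6 to that list by section number, so that the 10-day bar covers every listed drug.

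Minor alignments to make at the same time:
- QTc of 500 ms or more in both places.
- Reword the Summary's potassium line to match 5.1.2.2: exclude on an available pre-inclusion result, otherwise act on the same-day inclusion sample.
- State in 5.3.4 that the action covers potassium above 5.5 as well as below 3.5 mmol/L.

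The cost is a short amendment and an eCRF check. Compared with 5.1.2 as written, eligibility narrows by an amount that the protocol does not allow us to estimate. There is no effect on alpha or on the primary intention-to-treat analysis.
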